#### **10.7. Safety Analysis**

Adverse events will be described on treatment and during follow-up. AEs will be coded using MedDRA and tabulated by severity / CTC V4 AE grading. Causality of AEs will also be tabulated. Serious Adverse Events will be described by individual narratives based on the SAE reports provided by the site investigators. Summary statistics will be tabulated for hematological and biochemical parameters as well as for efficacy of ART (CD4 count, viral load) at each time point.

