| 
Study Duration
 | 
Treatment duration will be 28 days or 56 days in case of extended treatment (please refer to point b).
 
 
a) If at day 29 assessment, tissue aspirate is parasite negative, the patient will be eligible for secondary prophylaxis* and enter the of one-year follow-up phase (i.e. day 58, 210 and 390 assessments) following initial treatment.
 
b) If at day 29 assessment, tissue aspirate is parasite positive and the patient is well (i.e. no fever and clinical improvement of VL signs and symptoms compared to baseline), s/he will receive another complete course of the same treatment. (Note: these patients will still be considered treatment failures at the primary endpoint).
 
c) If at day 29 assessment, tissue aspirate is positive and the patient is unwell, s/he will also be considered a treatment failure, but the patient will be treated with a rescue therapy.
 
 
Patients who have an extended treatment (option b) will be evaluated on day 58. Those who still have a parasite positive tissue aspirate at this assessment will be offered a rescue treatment. Those who are negative at this assessment will be evaluated a month later (i.e. day 86) to assess their eligibility to start secondary prophylaxis. *
 
Patients who have rescue treatment (option c) will be evaluated on day 58. Those who still have a parasite positive tissue aspirate at this assessment may be offered another rescue treatment. Those who are negative will be offered secondary prophylaxis, if eligible. *
 
All patients, independently of their outcome at day 29 and/or day 58, will enter the follow-up assessments (i.e. day 210 and 390 assessments).
 
All patients who are not yet on antiretroviral treatment (ART) will commence ART once they have completed the routine VCT procedures. This will be approximately 2-3 weeks after commencement of VL treatment. Those who are still critically ill according to clinical judgment of the attending physician will have ART deferred until clinical improvement. Patients who are already on ART at diagnosis of VL will continue ART throughout the study. The ART treatment will be provided to the patient through the Ethiopian ART programme before (if applicable), during and after the study.
 
* Secondary prophylaxis given will be pentamidine 4mg/kg IM once a month. Patients will be eligible for this if their CD4 count is < 200 cells/mL and there is no contraindication (e.g. renal failure, diabetes mellitus, known hypersensitivity) for the drug used. Secondary prophylaxis will normally be continued until the patient has sufficient CD4 recovery (over 200 cells/mL at day 390 assessment). However, it would be stopped in case of relapse, adverse events requiring discontinuation of medication or if the patient requests to stop the prophylaxis.
 |

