#### **Safety**

Assessment of safety during treatment and follow-up based on clinical adverse events, laboratory parameters during treatment and 1 month (after end of initial treatment or after end of extended treatment) follow-up.

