#### **3.2. Study duration and duration of subject participation**

There will be two recruitment sites in Ethiopia (i.e. Gondar, Abdurafi). Additional sites may be considered in the event that patient recruitment takes longer than expected.

The overall study duration is expected to be 30 months, from start of recruitment to final assessment (12 months follow-up) of last patient and at least 18 months is estimated for the recruitment period.

All patients will be hospitalized for approximately 30 days (including baseline assessments and initial treatment period). However, if the tissue aspirate performed on day 29 is positive and the patient is clinically well (i.e. no fever and clinical improvement of VL signs and symptoms compared to baseline), a complete course of the same treatment will be given and the hospitalization will be prolonged until day 58.

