### **8.7.3. Eliciting Adverse Event information**

The investigator is required to report all directly observed adverse events and all adverse events spontaneously reported by the trial subject using concise medical terminology. In addition, each trial subject will be questioned about the occurrence of adverse events on a daily basis during the hospitalization period (day 0-29; or until day 58 in case of extended treatment), and 1 month after the stop of treatment (i.e. day 58 or day 86 in case of extended treatment) with a generic question such as “have you felt different in any way/ had any problems since starting the new treatment/the last assessment?” If the response is “Yes”, the nature of the event, the date and time (where appropriate) of onset, the duration, maximum intensity (see below) and relationship to treatment will be established (see below). Details of any

dosage/schedule modification or any corrective treatment will be recorded on the appropriate pages of the CRF.

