#### **8.7.4. Adverse Event reporting period**

The adverse events reporting period for this trial begins:

- Upon administration of the first dose of study medication for non-serious and serious events and ends 1 month after the stop of the treatment when a further safety evaluation occurs.

All adverse events that occur during the adverse event reporting period specified in the protocol must be reported to DNDi, whether or not the event is considered related to study medication.

In case a patient receives the secondary prophylaxis, there will be another period of safety reporting. The reporting period starts upon administration of the first dose of Pentamidine up to a week after the last injection of Pentamidine that occurs during the study period. Only Serious Adverse Events will be collected during this period.

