#### **8.7.6. Grading of Adverse Event severity**

Clinical adverse events and laboratory parameters will be graded by investigator using the Common Toxicity Criteria for Adverse Events (CTC AE) version 4 (May 2009) so that comparisons can be made between treatment arms. This specific

adverse event severity grading scale is used in order to standardize reporting between investigators and sites.

In the case that an AE is not listed, the assessment of intensity/severity will be based on the investigator's clinical judgment. The maximum intensity/severity experienced should be recorded and will be assigned to one of the following categories.

- MILD - Does not interfere with patient's usual functions
- MODERATE - Interferes to some extent with patient's usual functions
- SEVERE - Interferes significantly with patient's usual functions

It is to be noted the distinction between severity and seriousness of adverse events. A severe adverse event is not necessarily a serious event.

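### On-treatment adverse events are counted over 28 or 56 days depending on the day-29 aspirate, which raises crude percentages and worst grades in the arm with more extended courses

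*Protocol*

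**What the plan says.** The length of treatment is set in the Synopsis (Study Duration): "Treatment duration will be 28 days or 56 days in case of extended treatment". Section 3.2 says who gets the longer period. If the day-29 aspirate is positive and the patient is clinically well, "a complete course of the same treatment will be given and the hospitalization will be prolonged until day 58". The same aspirate is the primary endpoint (section 2.2.1).

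The collection of adverse events follows that split:

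- Section 8.7.3 has patients questioned "on a daily basis during the hospitalization period (day 0-29; or until day 58 in case of extended treatment"), and then once more "1 month after the stop of treatment (i.e. day 58 or day 86 in case of extended treatment").
- Section 8.7.4 says that the reporting period "ends 1 month after the stop of the treatment when a further safety evaluation occurs".
- The safety endpoint in section 2.2.2 runs to "1 month (after end of initial treatment or after end of extended treatment) follow-up".
- Section 8.7.5 has each event entered in the CRF once per patient, at its worst grade, with a count of episodes if it recurs.

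On analysis, section 10.7 says only "Adverse events will be described on treatment and during follow-up", with tabulation by grade and by causality. Section 8.7.6 gives the reason for a common grading scale: "so that comparisons can be made between treatment arms". Section 10.9 has the DSMB review adverse events for both arms at each look.

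Patients who are positive and unwell at day 29 go to rescue treatment (Synopsis; section 7.9). Their rescue course falls in the month that would otherwise be follow-up. No section says under which heading their events are then tabulated.

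**The concern.** A patient cleared at day 29 contributes one course and about four weeks of daily questioning to the on-treatment column. A patient who is positive but well contributes two courses and about eight weeks. If the arms differ in the number of such patients, the crude on-treatment percentages differ even when the regimens are equally safe. The longer period gives more time for a first event, and the single worst-grade record carries the effect into the severity table.

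The overall objective is a regimen that is both safe and effective, and safety is a secondary objective. If part of the efficacy result feeds into the safety table, a reader of that table may take a difference in cure for a difference in toxicity.

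**Working it through.** **The plan's own figure.** The protocol states no adverse-event rate. Its one computed design figure, 66 per arm and 7 looks, uses the cure rates adopted below (0.75 and 0.90), and it reproduces.

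- theta = ln[0.90 × 0.25 / (0.75 × 0.10)] = ln 3 = 1.0986
- a = (2/theta) × ln(1/(2 × 0.05)) = 4.192; slope c = theta/4 = 0.2747; information per patient = 0.75 × 0.25 = 0.1875
- Correction for looks every 10 patients: 4.192 − 0.583 × sqrt(10 × 0.1875) = 3.394
- Maximum n = 3.394 / (0.2747 × 0.1875) = 65.9, so 66 patients and 7 looks

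**Inputs for the safety check**

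- From the protocol: treatment of 28 or 56 days; reporting to day 58 or day 86; cure of 0.75 in one arm and 0.90 in the other (the design values, used as an illustration).
- Assumed: w, the share of day-29 failures who get the extended course, the same in both arms, from 0 to 1; q, the risk of at least one event in 28 days, from 20% to 50%; the same constant hazard in both arms.

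**Length of the period.** Let e = (1 − cure) × w be the extended share of an arm. Mean treatment time = 28 + 28e.

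- w = 1: e = 0.25 v 0.10, giving 35.0 v 30.8 days (ratio 1.14)
- w = 0.5: e = 0.125 v 0.05, giving 31.5 v 29.4 days (ratio 1.07)
- w = 0: 28 v 28 days

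The mean reporting period is 58 + 28e, or 65.0 v 60.8 days at w = 1. The part after treatment stops is about one month on either schedule (day 29 to 58, or day 58 to 86).

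**Crude on-treatment percentage.** (1 − e)q + e[1 − (1 − q)²] = q + e × q(1 − q). The gap between arms is therefore (e1 − e2) × q(1 − q).

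| q | w = 1, 75% v 90% cure | Gap, w = 1 (points) | Gap, w = 0.5 (points) |
|---|---|---|---|
| 20% | 24.0% v 21.6% | 2.4 | 1.2 |
| 30% | 35.25% v 32.1% | 3.15 | 1.6 |
| 50% | 56.25% v 52.5% | 3.75 | 1.9 |

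Because q(1 − q) is at most 0.25, the gap at these cure rates cannot exceed 0.15 × 0.25 = 3.75 points for any q, and it is 0 at w = 0. For a wider contrast of 60% v 90% (the Synopsis cites 60% overall cure on 30 mg/kg monotherapy), the gap at w = 1 is 0.30 × q(1 − q), or 4.8 to 7.5 points over the same q.

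**Scale.** At 66 per arm and 30% incidence, the standard error of a difference is sqrt(2 × 0.3 × 0.7 / 66) = 8.0 points.

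**With a common period.** Over first dose to day 29, e drops out: both arms show q and the gap is 0. An event rate per patient-day at constant hazard is also equal in the two arms.

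The protocol gives no grade-specific risks, so the effect on worst grade has the same direction but cannot be sized.

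**The case against.** The strongest reply is that section 10.7 is a short descriptive outline. It plans no rate, contrast or test. Windows and denominators usually belong to the statistical analysis plan, which is not at hand. Onset dates are collected (section 8.7.3), so a day-29 cut of incidence stays possible. The safety endpoint also covers extended treatment on purpose, and toxicity of a second course is useful information. All of this stands, and it keeps the point modest. Two things remain. The protocol itself fixes a collection period that depends on outcome and gives between-arm comparison as a purpose of grading. And onset dates do not recover the grade reached by day 29 once section 8.7.5 has reduced repeat episodes to one worst-grade entry.

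A reader might infer more than the text supports:

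- **That follow-up percentages also differ because follow-up is longer in one group.** It is about one month on both schedules. What differs is content: after one course, after two, or under rescue.
- **That the less effective arm must look more toxic.** Section 10.6 also counts deaths and withdrawals as failures, and these can shorten questioning. The push is towards the arm with more extended patients, which need not be the arm with fewer cures.
- **That rescue toxicity is charged to study drug.** The protocol does not say so. Causality is assessed with other medication considered (section 8.7.7) and is tabulated.
- **That follow-up should be censored at rescue.** This would remove events in the sickest patients soon after study drug, and section 1 notes miltefosine's long half-life. Delayed toxicity could be hidden.

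**Conclusion.** The point holds in a limited form. Crude on-treatment percentages and worst grades by arm depend on how many patients have an extended course, and so partly on the primary endpoint. At cure of 75% v 90% the artefact in the percentage is 0 to about 3.75 points, below the sampling error of about 8 points. It is systematic, though, and more patients would not remove it.

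The range rests on equal constant hazard in both arms, a common share of failures extended, and an assumed 28-day event risk. If the share extended differs between arms, the gap can be larger or reversed. A day-29 table has no such artefact, and nor has a rate per patient-day if the hazard is constant.

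**What to change.** In section 10.7 and the matching Synopsis paragraph:

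- Make adverse events from first dose to day 29, by randomised regimen, the main between-arm safety table.
- Tabulate events during the extended course, and events after the start of rescue, in separate tables with patient-days as denominator. Drop and censor none of them.

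In section 8.7.5 and the CRF, record the grade by course, so that second-course severity does not enter the day-29 table through the single worst-grade record.

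The cost is a few more tables and one more CRF field. Patient care and visits do not change.

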#### **10.8. Analysis of other endpoints**

Other parameters including pharmacokinetics, microarray and cytokine, immunoglobulin levels will be analyzed and reported independently. A summary of results will be included as an appendix to the final clinical study report.

#### **10.9. Interim analysis**

There will be sequential analysis every 20 patients (10 patients in each arm), up to completion of the study. A maximum of 7 analysis will be performed. DSMB will consider if both treatment arms should be continued based on pre-defined criteria set in the sequential analysis. DSMB will also review the available safety data (AEs, SAEs) for both treatment arms.

In order for the findings of this study to be generalizable the population included in this study is heterogeneous (i.e. includes relapse and primary VL patients, patients currently on ART and those that will start ART). In order to address potential concerns regarding the heterogeneity of the population and reduce the likelihood of rejecting a treatment that may be effective in a sub section of the population a test to assess heterogeneity will be performed when a treatment is stopped. This test will be

conducted to verify on the available data if there is a signal of interaction ( $p < 0.10$  = possible interaction) between strata (primary VL or relapse; patients currently on ART or patients initiated on ART during the study) and treatment (magnitude of the treatment effect is dependent upon strata). In absence of signal of interaction ( $p > 0.10$ ) the magnitude of the difference in success rates between treatments should be relatively homogeneous across strata. In presence of significant signal interaction, the treatment effect will have to be adjusted on strata to know whether both therapeutic strategies have the same success rate. Depending on the outcome of this test for heterogeneity, recruitment may be continued into one stratum. This decision will be taken by the sponsor following consultation with the DSMB and other relevant authorities.

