| 
Statistics
 
Summary of analysis
 | 
Primary Endpoint Analysis: Day 29
 
The study is designed and will be analysed according to group-sequential methods, specifically the triangular test. The triangular test is one way of analysing group sequential trials and uses straight line stopping boundaries. It involves analysing the data as they accumulate, with points being plotted relative to a triangular region and stopping when the upper or lower boundary of the region is crossed (Graph 1). It has the advantage over other methods of analysing group sequential trials, such as the discrete sequential probability ratio test, in that a closed continuation region is used ensuring that the trial stops within a pre-specified maximum sample size.
 
The type I error rate and power of the study were set to 5% and 95%, respectively (<math>\alpha=0.05</math>, <math>\beta=0.05</math>) with parameters <math>p_0=0.75</math> and <math>p_a=0.90</math>. Based on these specifications, the boundaries of the test were calculated for the null hypothesis, <math>H_0: p \leq p_0</math>, and the alternative hypothesis, <math>H_a: p > p_0</math> (see Graph 1). Based on the rationale above, rejecting the null hypothesis, <math>H_0: p \leq p_0</math>, (crossing the upper boundary) means that we can consider the regimen for compassionate use while failing to reject the null hypothesis (crossing the lower boundary) means that we cannot consider the regimen for compassionate use. Data from each arm will be analysed (for the evaluable patient population or per protocol analysis) after every 10 patients reach the primary endpoint of initial cure, where the actual values of Z and V will be calculated and then plotted on the graph. Depending on where the point falls, that arm of the trial will either continue collecting data for another 10 patients or will stop, concluding with a rejection of the null hypothesis (adequate efficacy) or a non-rejection of the null hypothesis (inadequate efficacy). In the final analysis, asymptotic properties will be used to calculate unbiased estimators of the response rate and its 95% confidence interval taking into account the sequential nature of the analyses.
 
Secondary Endpoint Analysis:
 
When the analyses concludes that an arm should be stopped (i.e. a boundary has been crossed), survival at 1 year will also be evaluated. Due to sequential design employed and the different treatment options to be determined by day 29 outcomes (i.e. repeat treatment and/or pentamidine prophylaxis), subsequent analyses (i.e. the secondary endpoint) are likely to be descriptive only. Such descriptive analyses will focus on survival (alive and disease-free) at 12 months post day 29 assessment and relapses between day 29 and 12 months follow-up, by arm and day 29 outcome.
 
Safety Analysis
 
Adverse events (AEs) will be described on treatment and during follow-up. AEs will be coded using MedDRA and tabulated by severity / CTC V4 AE grading. Causality of AEs will also be tabulated. Serious Adverse Events (SAEs) will be described by individual narratives based on the SAE reports provided by the site investigators. Summary statistics will be tabulated for haematological and biochemical parameters as well as for ART efficacy (CD4 count, viral load) at each time point.
 |

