#### **3.3. Rationale of study design**

Although WHO recommends Ambisome® 40 mg/kg for HIV VL co-infected patients, this is based on limited information from Mediterranean countries; there are no data available from Ethiopia and there is little information available on the efficacy of the test treatments and no established standard treatment with a proven efficacy (of at least 90%) in East Africa. It is therefore not possible to design a comparative study as there is insufficient data to set margins for superiority or non-inferiority. The design of the study will therefore focus on establishing efficacy of two potential test treatments for VL in HIV co-infected individuals.

Recent practice by MSF in their treatment centre at Abdurafi using Ambisome® 30 mg/kg demonstrated a cure rate of only 74% in primary VL cases and of 38% in relapse cases. Increasing the dose to 40 mg/kg seems reasonable to achieve better cure rates. There are no other realistic options for monotherapy with the drugs that are currently available. SSG is too toxic and miltefosine while better tolerated is less effective than SSG as monotherapy.

Combination regimens are attractive as they offer potential added effects; preliminary experience from MSF using Ambisome® 30 mg/kg with miltefosine for 28 days increases the initial cure rate in relapse cases to 87%, while in primary VL this remains at 74%. Moreover, the combination seems to be well tolerated. This study aims to identify a treatment regimen is safe and effective for all HIV VL co-infected patients in both primary and relapse cases. While including primary and relapse cases makes the study population more heterogeneous, the outcome of the trial could be applicable to all cases that present. In the final analysis, cure rates for both arms will be stratified in both arms to see differences between primary cases and

relapses. The study will not be powered to detect statistically different differences as for this the sample size would have to be unrealistically much larger.

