## 10. Data Analysis and Statistical Methods

### 10.1. Sample size determination

The sample size will be determined according to the sequential design for the primary outcome to be measured at day 29.

Since we are using a sequential approach, the sample size is not defined or known in advance. The maximum sample size needed per arm would be 66 patients (132 total patients) and the maximum analyses performed would be 7 (see Graph 1, upper horizontal axis). The actual sample size may be less than this, with its value depending on the value of the proportion cured.

Graph 1: Triangular region for study arms showing the boundaries for analysing the sequential trial using the Triangular Test, with the following parameters ( $p_0 = 0.75$ ,  $p_a = 0.9$ ,  $\alpha = 0.05$ ,  $\beta = 0.05$  and  $n = 10$ ).

[figure not shown]

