### **10.6. Efficacy Analysis**

The primary and secondary endpoints have been described in section 2.2.

The primary endpoint (day 29) analysis will be defined as follows:

- Treatment success: absence of parasites on day 29; hence no rescue medication provided up to this time-point.
- Treatment failure: presence of parasites at day 29 *or* requirement of rescue medication due to lack of clinical improvement/ response *or* withdrawn from the study (e.g. due to a treatment limiting adverse event/ patient absconded) *or* death.

The data will be analysed as proportions according to an intention to treat and per protocol analysis for each treatment arm.

The secondary endpoint (12 months post treatment) analysis will be defined as follows:

- Treatment success: treatment success at day 29 or at day 58 in case of extended treatment and patient being alive and disease free (absence of signs and symptoms of VL or if symptomatic, a negative parasitological assessment by tissue aspirate) at day 390.
- Treatment failure: presence of signs of symptoms of VL, confirmed by presence of parasites in a parasitological investigation. It is mandatory that all patients who have possible presence of the disease have a parasitological assessment (a spleen aspirate or a bone marrow aspirate if the spleen is not palpable).

The primary endpoint will be analyzed following Whitehead (1983) including point and interval estimation of the proportion cured in each treatment arm.

Additional analyses will be conducted to evaluate potential differences in response to treatment between relapse versus primary VL cases, and patients that have previous exposure to ART or not. This will be done at the final sequential analysis (when we reach 66 per arm) and after one year follow up. A detailed description will be included in the statistical analysis plan.

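### The Section 10.9 heterogeneity test compares arms across strata, while each arm is stopped on its own cure rate, so it can miss a stratum worth rescuing

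*Protocol*

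**What the plan says.** The Synopsis and Section 10.1 set up a separate triangular test in each arm of a cure rate of at most 75% against an alternative of 90%. "The type I error rate and power of the study were set to 5% and 95%, respectively". Section 3.3 explains the lack of a between-arm test: "It is therefore not possible to design a comparative study". Crossing the lower boundary means that the arm's regimen is not carried forward.

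Section 10.9 adds a safeguard for the mixed population. To "reduce the likelihood of rejecting a treatment that may be effective in a sub section of the population a test to assess heterogeneity" is planned at the point where an arm stops. The test looks for an interaction between treatment and stratum, with p below 0.10 as a signal. Without a signal, the gap in success between the two treatments is taken to be similar across strata. With one, the treatment effect is adjusted for stratum to see whether the two strategies succeed equally often. The strata are primary versus relapse, and "patients currently on ART or patients initiated on ART during the study". Then: "Depending on the outcome of this test for heterogeneity, recruitment may be continued into one stratum", by sponsor decision after consulting the DSMB.

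Section 10.6 plans analyses by primary/relapse and by previous ART exposure. On timing it says: "This will be done at the final sequential analysis (when we reach 66 per arm) and after one year follow up".

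**The concern.** The purpose and the test do not match. A regimen is rejected because its own pooled cure rate is too low. It deserves a second look if that low rate is an average of a good stratum and a poor one, which is a contrast within the stopped arm. The interaction test contrasts the two arms, the comparison that Section 3.3 says the trial cannot be designed for.

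Two errors follow. If both regimens do well in primary and badly in relapse cases, there is no interaction and no signal. If the stopped arm is uniform and only the other arm varies, a signal appears although the stopped arm has no better stratum. The result informs whether a regimen is dropped or recruitment continues in one stratum.

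Three looser points sit alongside. The ART groups are worded differently in Sections 10.6 and 10.9. The two sections time the stratum analysis differently. Section 10.9 gives no boundary for a stratum that continues.

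**Working it through.** **Reproducing the design.** Inputs: null 0.75, alternative 0.90, α = β = 0.05, looks every 10 patients per arm (Synopsis, Sections 10.1 and 10.9).

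- θ = ln[(0.90 × 0.25)/(0.75 × 0.10)] = ln 3 = 1.0986
- a = (2/θ) ln(1/(2 × 0.05)) = 4.192; slope c = θ/4 = 0.2747; information per patient 0.75 × 0.25 = 0.1875
- Correction for discrete looks: a′ = 4.192 − 0.583 × √(10 × 0.1875) = 3.394
- Maximum n = (3.394/0.2747)/0.1875 = 65.9, i.e. 66, with looks at 10 to 70, hence 7. This matches the protocol: "The maximum sample size needed per arm would be 66 patients (132 total patients".
- Exact binomial recursion on these boundaries gives a false-success rate of 0.041 at 75%.

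**What each contrast measures** (percentage points; stopped arm A, other arm B; primary/relapse):

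| True cure rates | Within arm A | Interaction (A − B in primary, minus A − B in relapse) |
|---|---|---|
| A 92/45, B 92/45 | 92 − 45 = 47 | (92 − 92) − (45 − 45) = 0 |
| A 70/70, B 60/95 | 0 | (70 − 60) − (70 − 95) = 35 |
| A 74/38, B 74/87 | 74 − 38 = 36 | (74 − 74) − (38 − 87) = 49 |

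Only the third row uses protocol figures (Section 3.3: AmBisome 30 mg/kg alone, and the combination). The first two are assumed illustrations. The primary share is taken from the series in the Synopsis: 116/195 = 59%.

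**How often each test signals.** Trials were simulated with the boundaries above. When arm A stopped for inadequate efficacy, likelihood-ratio tests were applied at p < 0.10.

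| Scenario | Interaction test | Within-arm test |
|---|---|---|
| 92/45 in both arms | about 14% | about 87% |
| 90/50 in both arms | about 14% | about 79% |
| A 70/70, B 60/95 | about 50% | about 12% |
| A 74/38, B 74/87 | about 48% | about 47% |

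In the first row the pooled rate is 0.595 × 0.92 + 0.405 × 0.45 = 0.73. The arm stops for inadequate efficacy about 98% of the time, at a mean of 28 patients. The 14% is close to the test's false-positive rate at these sizes.

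The form of the interaction test does not change the picture. With 90/50 in both arms and 20 to 40 patients per arm, odds-ratio and risk-difference versions signal in 4–11%. A within-arm test signals in 55%, 76% and 88% at 20, 30 and 40.

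**Timing in Section 10.6.** The exact chance that an arm reaches the seventh look, the one that takes it to 66, is 1.2% at a true rate of 0.75, 3.5% at 0.90, and at most 7.3% (near 0.85).

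**Continuing one stratum.** The protocol gives no rule, so one was assumed: all rates 75%, continue in the better-looking stratum after a signal, apply the same boundaries. Reusing that stratum's accrued data raises false success per arm from about 4% to 5.8–5.9%. Using only new patients gives 4.7%, or 5.1% if the other arm is 74/95. Where the ART factor enters, half the patients were assumed to be on ART at entry; the protocol gives no figure.

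**The case against.** The strongest reply is that the protocol's own data do not look like the damaging case. Section 3.3 reports 74%/38% for AmBisome alone and 74%/87% for the combination, so relapse cases fare worse on one and better on the other. An interaction test picks that up about as often as a within-arm test. A reader might infer that the safeguard is useless. The documents do not support that: it fails for a shared stratum pattern and misfires when only the other arm varies. Section 3.3 also plans stratified cure rates for both arms in the final analysis, and a p-value does not bind the sponsor's decision. This stands and limits the severity, but does not make the specified test fit its stated purpose.

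Three further inferences go too far.

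- **The ART comparison is biased by survival.** This follows only from the literal wording. The same paragraph of Section 10.9 also speaks of patients who are going to start ART, so a split at entry was probably meant. What stands is that the wordings need reconciling.
- **Reopening breaks the 5% error rate.** The excess is under one point and needs an assumed data-reuse rule. Stratum boundaries may be set in an SAP that is not at hand.
- **The subgroup analysis will almost never be done.** Section 10.6 also schedules it after one year, which happens whatever the number of looks.

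The within-arm remedy has limits too. With 92/45, the exact 95% interval for primary cases excludes 75% in only about a quarter of futility stops; 16 of 17 cured has a lower limit of 71%.

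**Conclusion.** The mismatch is real and lies in the protocol's own wording. Section 10.9 tests a between-arm contrast to protect against an error that arises within one arm. Under a shared pattern (assumed 92%/45%, 59% primary) it signals in about 14% of futility stops, against about 87% for the right contrast. With a flat 70% arm beside a 60%/95% arm it signals about 50% of the time with nothing to rescue. On the protocol's own figures it signals in about 48%. These percentages rest on the reconstructed boundaries, the assumed rates and the primary share of the cited series; the direction follows from the contrasts alone.

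The ART definition and the 66-per-arm trigger are secondary wording faults. The inflation from continuing one stratum is modest, about 4% to 6% under an assumed reuse rule. The primary endpoint, the boundaries and the per-arm decision are unaffected. Severity: SHOULD-FIX.

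**What to change.** - **Section 10.9, test.** When an arm stops for inadequate efficacy, test the stratum effect within that arm at the 10% level. Report each stratum's cure rate with an exact confidence interval against 75%, and state that it will often be too wide to show that a stratum meets the target. Any between-arm interaction should be descriptive.
- **Sections 10.6 and 10.9, ART.** Define the stratum once, by ART status at randomisation. Read literally, the Section 10.9 wording omits patients who die or have ART deferred before starting, and it differs from the previous-exposure split in Section 10.6.
- **Section 10.6, timing.** Replace the 66-per-arm trigger with the point at which each arm stops, and keep the one-year analysis.
- **Section 10.9, continuation.** Either label continued recruitment in one stratum as exploratory, or test it on newly enrolled patients only, with its own boundary.

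The cost is wording; the data are already collected. The downside is that, under a confirmatory continuation, the patients who triggered it cannot be reused, so that stratum needs more recruits.
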